#### Individual Subject Stopping Criteria

Dosing for the subject will be temporarily discontinued and DSMB will be informed (at a minimum) if any of the following occur:

- Any treatment emergent adverse event (TEAE) at least Grade 3 (according to the most current version of the CTCAE) assessed by the PI determined to be related to the study drug
- Any two TEAEs Grade 2 experienced by the same subject within one week (according to the CTCAE) including 2 symptomatic hypotension events within one week (non-urgent medical intervention indicated) or any Grade 3 hypotension event (medical intervention or hospitalization indicated) assessed by the PI. Two grade 2 injection site reactions such as presence of swelling at the injection site will not require urgent reporting to the DSMB or subject suspension as long as no further intervention was required.
- Prolongation of QTcF (QT corrected Fredericia) interval to more than 500 msec, ventricular tachycardia greater than five beats
- Any clinically significant worsening of existing disproportionate growth, as determined by physical measurement ratios and/or PI assessment based on measurement or clinical observation findings
  - o Sitting height to standing height ratio – Worsening of ratio of more than 1 standard deviation from initiation of therapy based on NHANES data .
  - o Arm span minus height – Worsening of more than 1 standard deviation since initiation of therapy with a SDS either >+2 or <-2. Data is based on Gerver et al.
- Excessively rapid increase in growth velocity (defined as greater than the 90th percentile on age- and gender-specific growth charts) sustained over a period of 2 years or associated with an adverse event such as joint pains or deformity 
- Clinically significant worsening of scoliosis as observed via clinical or radiographic assessment. This is defined as a new onset asymmetry noticed during a forward bend test or an increase in Cobb angle of >10 degrees from baseline or any Cobb angle of >20 degrees at any point in the study.

Subjects may continue in the extension phase of the study until achieving near final adult height which will be defined as either:

- A growth velocity <1.5 cm/year over the prior 12 months
- A bone age via the Greulich and Pyle method of 13 years in females and 15 years in males.

After PI consultation with the DSMB, the subject may be re-challenged with a 20% dose reduction for any AE which may be dose related and is reversible with dose decrease (such as hypotension). If excessive increase in growth, worsening of scoliosis or other conditions related to bone overgrowth are noted, vosoritide will be discontinued permanently, and the subject will be followed-up off treatment for the duration of the study. If the subject meets stopping criteria on re-challenge or if the subject refuses re-challenge, the subject will be permanently discontinued from the medication with ongoing assessment in the study.

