g PD: Samples will be obtained for urinary cGMP at baseline at the Screening Visit and at baseline and 1 hour, 2 hours and 4 hours post vosoritide injection at the Day 1 Visit, 6 Month Visit and 12 Month Visit. Urine creatinine samples will be obtained at all of the same time points. Serum collagen X marker measurement will be obtained at baseline at the Screening Visit, Day 1 Visit, 6 Month Visit and 12 Month Visit.

h DXA scan will include whole body less head as well as a lumbar spine DXA. If the DXA is unable to be completed on Day 1, it may be completed on Day 2.

i Spine X-rays will include an posteroanterior view of the spine. If the spine X-ray is unable to be completed on Day 1, it may be completed on Day 2. If the clinical examination suggests a new onset spine asymmetry, an additional spine X-ray will be performed at the 6 month visit.

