### Study Suspension Criteria

Dosing for all subjects will be temporarily discontinued and DSMB will be informed (at a minimum) if any of the following occur:

- Any two subjects with a TEAE at least Grade 3 (according to the most current version of the CTCAE) assessed by the PI to be related to study drug

- Any two subjects with two TEAEs Grade 2 experienced by the same subject within one week (according to the CTCAE) including 2 symptomatic hypotension events within one week (non-urgent medical intervention indicated) or any Grade 3 hypotension event (medical intervention or hospitalization indicated) assessed by the PI. Two grade 2 injection site reactions such as presence of swelling at the injection site will not meet this criterion as long as no further intervention was required.
- Any two subjects with prolongation of QTc interval to more than 500 msec, ventricular tachycardia greater than five beats
- Any two subjects with clinically significant worsening of existing disproportionate growth as defined above in the individual stopping criteria
- Any two subjects with excessively rapid increase in growth velocity (defined as greater than the 90th percentile on age- and gender-specific growth charts) sustained over a period of 2 years or associated with an adverse event such as joint pains or deformity which required discontinuation of study drug
- Any two subjects with clinically significant worsening of scoliosis as defined above in the individual stopping criteria
- Any other reason the DSMB advises temporary discontinuation of cohort dosing until further review of safety data is conducted

The DSMB will review available, relevant safety data within 5-7 days after the PI is apprised of an event. Based on its review, the DSMB may make any of the following recommendations:

- Continue dosing of subjects as planned with additional safety monitoring and/or safety reviews as indicated
- Decrease dose for all subjects
- Extend temporary treatment discontinuation until additional data are available and/or further review/consultation occurs
- Permanently discontinue treatment for all subjects

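### One limb of the scoliosis worsening rule is an absolute Cobb angle, so a stable curve above 20 degrees present before treatment meets the rule on the baseline film

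*Protocol*

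**What the plan says.** Among the individual stopping criteria in Section 7.1 is "Clinically significant worsening of scoliosis as observed via clinical or radiographic assessment". The next sentence defines this by three alternatives joined by *or*: new asymmetry on forward bending; "an increase in Cobb angle of >10 degrees from baseline"; or "any Cobb angle of >20 degrees at any point in the study".

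Two consequences follow in the same section.

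- For the child: "If excessive increase in growth, worsening of scoliosis or other conditions related to bone overgrowth are noted, vosoritide will be discontinued permanently". The rest of that sentence provides for follow-up off treatment until the end of the study.
- For the trial, under Study Suspension Criteria: "Dosing for all subjects will be temporarily discontinued and DSMB will be informed (at a minimum) if any of the following occur". One listed event is "Any two subjects with clinically significant worsening of scoliosis as defined above in the individual stopping criteria".

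The Schedule of Activities (Section 1.3) has no spine film in the screening column. The first is on Day 1, and its footnote adds: "If the spine X-ray is unable to be completed on Day 1, it may be completed on Day 2". Vosoritide is first given on Day 1. Neither the inclusion criteria (5.1) nor the exclusion criteria (5.2) mention scoliosis or a Cobb angle.

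**The concern.** The label names a change, and the first two limbs each describe one: a new finding, or an increase from baseline. The third describes a state. A child whose curve exceeded 20 degrees before any vosoritide, and has not moved since, satisfies it.

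That child can complete the six-month observation period, receive a first dose, and then fall under a permanent stop for a finding that predates treatment. Section 7.2 allows no replacement once a subject has been dosed, which matters when Section 9.2 aims for only about 10 children in each genetic cohort. Because the study-level rule adopts the individual definition, two such children would also interrupt dosing for all the others.

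**Working it through.** The plan states no trigger probability for this rule, so there is no figure to reproduce. The check is first one of wording, then an illustration.

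**Wording, set side by side**

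1. *Within the scoliosis rule.* The Cobb-increase limb is tied to baseline. The absolute limb is not, and its time window covers the whole study, so the baseline film falls inside it.
2. *Against the arm-span rule in the same list.* That rule needs both elements: "Worsening of more than 1 standard deviation since initiation of therapy with a SDS either >+2 or <-2". An out-of-range value alone does not trigger it. For scoliosis, an out-of-range value alone does.
3. *Against eligibility.* The nearest safeguard is exclusion 7 in Section 5.2, a clinically significant abnormality on screening tests in the investigator's judgement. The spine film is not a screening test. The note under Adverse Events in Section 8.2 lets the investigator add safety assessments but leaves out X-rays, so it does not supply an earlier film.
4. *Against film timing.* A Day 2 film follows the first dose. For a Day 1 film, the text does not require a reading before dosing.
5. *Against Section 8.3.4.* A condition present at screening is treated there as baseline, and becomes an adverse event only if it deteriorates. Under Section 7.1 the same stable curve is classed as worsening.

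**Illustration of size**

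Inputs: n = 75, the maximum in the synopsis; a trigger of two subjects, from Section 7.1; p, the share of treated children with a baseline angle above 20 degrees, which is an **assumption** because the documents do not give it. Children are taken as independent with a common p.

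P(at least one) = 1 − (1 − p)^75

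P(at least two) = 1 − (1 − p)^75 − 75·p·(1 − p)^74

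For p = 0.01: 0.99^75 = 0.471 and 75 × 0.01 × 0.99^74 = 0.357, so P(at least one) = 0.529 and P(at least two) = 0.173.

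| Assumed p | Expected number (75p) | At least one (individual stop) | At least two (dosing hold) | At least two if n = 35 |
|---|---|---|---|---|
| 0.5% | 0.38 | 0.313 | 0.055 | 0.013 |
| 1% | 0.75 | 0.529 | 0.173 | 0.048 |
| 2% | 1.50 | 0.780 | 0.444 | 0.155 |
| 5% | 3.75 | 0.979 | 0.894 | 0.528 |

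The last column uses the initial sample of 35 in Section 9.2, because 75 is a ceiling. If a stable baseline curve did not count as a trigger, the contribution of such curves would be zero by construction.

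**The case against.** **The limb may be a deliberate cap.** The QTcF limit of 500 msec in the same list is also absolute, and a fixed angle could be a cautious choice for a growth-promoting drug. That is possible, and whether such a child should be treated is a clinical matter. But a deliberate cap would not fit the label, the eligibility criteria or a first film that may follow dosing, so the passages would still need reconciling.

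**The word worsening may be meant to govern.** A sensible investigator might not stop a child for an unchanged curve. However, the protocol gives an express definition, and that makes the limb operative. Two investigators could decide the same case in opposite ways, with a permanent stop at stake.

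**Other filters exist.** A complete musculoskeletal examination is scheduled at screening and on Day 1, and the history must cover conditions bearing on participation or safety. These make an unnoticed large curve less likely, and this stands as a reason to treat the higher values of p with caution. None of them yields a Cobb angle or requires exclusion.

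**Stronger consequences that a reader might infer are not supported.**

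- *That primary endpoint data are lost.* Section 7.1 keeps the child in follow-up off treatment, and Section 9.3 analyses everyone who received at least one dose. The 12-month height is still due and still analysed. What is lost is time on drug.
- *That stable curves inflate the adverse-event counts.* Section 8.3.4 keeps a condition present at screening out of them unless it deteriorates. The problem lies in the stopping triggers.
- *That two such children end the trial.* The hold is temporary. The DSMB reviews within 5 to 7 days and may recommend continuing as planned with added monitoring.

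**Conclusion.** The point holds as an inconsistency in wording with mandatory consequences. Applied literally, Section 7.1 permanently stops drug in a child with a stable pre-treatment curve above 20 degrees, and two such children cause a temporary hold for all. This does not depend on prevalence: one child is enough for an individual stop.

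How often it would happen cannot be established from the documents. With 75 treated children, the chance of a hold from baseline curves alone runs from about 5.5% at an assumed 0.5% to 89% at an assumed 5%. That range shows sensitivity to the assumption and is not a forecast. With fewer than 75 treated, or with informal screening that removes visible curves, the values would be lower.

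**What to change.** Reconcile five things: the worsening label and the absolute limb in Section 7.1; the eligibility criteria in Section 5.2; the timing of the first spine film in Section 1.3; the permanent individual stop; and the two-subject dosing hold that adopts the same definition. The amended text should state whether a curve already present on the baseline film is a trigger for each of the two consequences, and should agree with the treatment of pre-existing conditions in Section 8.3.4. Which clinical rule applies is for the sponsor, and none is proposed here.

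The cost is a protocol amendment to wording in Section 7.1, extending to 5.2 or 1.3 only if the sponsor's decision requires it. The reconciliation itself needs no new procedure and no change to the sample size.

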### Study Suspension Criteria

Dosing for all subjects will be temporarily discontinued and DSMB will be informed (at a minimum) if any of the following occur:

- Any two subjects with a TEAE at least Grade 3 (according to the most current version of the CTCAE) assessed by the PI to be related to study drug

- Any two subjects with two TEAEs Grade 2 experienced by the same subject within one week (according to the CTCAE) including 2 symptomatic hypotension events within one week (non-urgent medical intervention indicated) or any Grade 3 hypotension event (medical intervention or hospitalization indicated) assessed by the PI. Two grade 2 injection site reactions such as presence of swelling at the injection site will not meet this criterion as long as no further intervention was required.
- Any two subjects with prolongation of QTc interval to more than 500 msec, ventricular tachycardia greater than five beats
- Any two subjects with clinically significant worsening of existing disproportionate growth as defined above in the individual stopping criteria
- Any two subjects with excessively rapid increase in growth velocity (defined as greater than the 90th percentile on age- and gender-specific growth charts) sustained over a period of 2 years or associated with an adverse event such as joint pains or deformity which required discontinuation of study drug
- Any two subjects with clinically significant worsening of scoliosis as defined above in the individual stopping criteria
- Any other reason the DSMB advises temporary discontinuation of cohort dosing until further review of safety data is conducted

The DSMB will review available, relevant safety data within 5-7 days after the PI is apprised of an event. Based on its review, the DSMB may make any of the following recommendations:

- Continue dosing of subjects as planned with additional safety monitoring and/or safety reviews as indicated
- Decrease dose for all subjects
- Extend temporary treatment discontinuation until additional data are available and/or further review/consultation occurs
- Permanently discontinue treatment for all subjects

## 7.2 PARTICIPANT DISCONTINUATION/WITHDRAWAL FROM THE STUDY

Subjects (or their legally authorized representative) have the right to withdraw their consent to participate in the study at any time without prejudice. The Investigator must withdraw from the study any subject who requests to be withdrawn. A subject's participation in the study may be discontinued at any time at the discretion of the Investigator and in accordance with his/her clinical judgment. When possible, the tests and evaluations listed for the termination visit should be carried out.

Reasons for which a subject may be withdrawn from the study or from study treatment by the Investigator include but are not limited to the following:

- Subject experiences a serious or intolerable AE
- Subject develops a clinically significant laboratory abnormality
- Subject requires medication or medical procedure prohibited by the protocol
- Subject does not adhere to study requirements specified in the protocol
- Subject was erroneously admitted into the study or does not meet entry criteria
- Subject is lost to follow-up

Subjects may continue in the extension phase of the study until achieving near final adult height which will be defined as either:

- A growth velocity <1.5 cm/year over the prior 12 months

- A bone age via the Greulich and Pyle method of 13 years in females and 15 years in males.

Non-adherence to study medication administration will be monitored via review of the medication administration log and counting of empty vials at the 6 and 12 month visits. Subjects will be encouraged to have 100% compliance with study drug administration. If during a 30 day period, a subject misses 5 or more shots, they will be considered non-compliant with the study protocol. They will be given a warning that compliance must improve or they will be withdrawn from the study. If there is a second 30 day period when the subject misses 5 or more shots, they will be withdrawn from the study.

The reason for participant discontinuation or withdrawal from the study will be recorded on the Termination Visit Case Report Form. Subjects who sign the informed consent form but do not receive vosoritide may be replaced. Subjects who sign the informed consent form, and receive vosoritide, and subsequently withdraw, or are withdrawn or discontinued from the study will not be replaced.

### 7.3 LOST TO FOLLOW-UP

A participant will be considered lost to follow-up if he or she fails to return for any in-person scheduled visits and is unable to be contacted by the study site staff.

The following actions must be taken if a participant fails to return to the clinic for a required study visit:

- The site will attempt to contact the participant and reschedule the missed visit as soon as possible and counsel the participant on the importance of maintaining the assigned visit schedule and ascertain if the participant wishes to and/or should continue in the study.
- Before a participant is deemed lost to follow-up, the investigator or designee will make every effort to regain contact with the participant (where possible, 3 telephone calls and, if necessary, a certified letter to the participant's last known mailing address or local equivalent methods). These contact attempts will be documented in the participant's study file.
- Should the participant continue to be unreachable, he or she will be considered to have withdrawn from the study with a primary reason of lost to follow-up.

## 8 STUDY ASSESSMENTS AND PROCEDURES

### 8.1 EFFICACY ASSESSMENTS

#### **Demographic Data and Medical History**

Demographic data and a detailed medical history will be obtained at Screening and again at the Day 1 visit. This medical history should elicit all major illnesses, diagnoses, and surgeries that the subject has ever had, and any prior or existing medical conditions that might interfere with study participation or safety.

#### **Measures of Medication Compliance**

The subject's caregiver will demonstrate proper medication preparation and administration technique at the Day 2 Visit. Any deficiencies will be corrected with additional education. Subjects will fill out a daily medication administration log. These will be reviewed during all telephone calls and in person at the 6 and 12 month study visits and all in-person extension phase visits. The log will be compared to the empty vial counts at the 6 and 12 month visits and all in-person extension phase visits.

#### **Parental Anthropometrics**

The standing height of the participant's biological parents will be assessed if they agree to participate. Both parents should be measured if available. If unavailable, report of the parents' heights will be recorded.

### **Subject Anthropometrics**

Anthropometric measurements include standing height, weight, sitting height, head circumference and arm span. Standing height should be measured 5 times using a calibrated stadiometer. The average of the 5 measurements will be used as the outcome measure. Sitting height should be measured three times using a seated stadiometer. The average of the 3 measurements will be used as the outcome measure. Weight should be measured on a digital scale. Head circumference and arm span will each be measured once using standard procedures. Sitting height ratio will be calculated as the sitting height divided by the standing height. Arm span minus standing height will also be calculated. All measurements will be performed in centimeters.

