#### **Endpoints:**

The primary study endpoints include:

- Incidence of adverse events per subject with particular attention to Grade 3 and 4 adverse events as well as to rates of hypotension
- Change from baseline in age-sex standardized annualized growth velocity after 12 months of treatment
- Change from baseline in age-sex standardized height SDS after 12 months of treatment

The secondary study endpoints include:

- Change from baseline in seated height ratio after 12 months of treatment
- Change from baseline in arm span minus standing height after 12 months of treatment
- Change from baseline in bone age/chronological age after 12 months of treatment

During the extension study, all of the endpoints will remain the same, but the timeframe will be extended from 12 months until growth cessation or subject withdrawal from the study.

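### Arm span is read once per visit although arm span minus height is a secondary endpoint and a dosing-stop measurement; averaging three readings would be a cheap gain in precision

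*Protocol*

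**What the plan says.** The measurement rules are in Protocol section 8.1, Subject Anthropometrics. For height: "Standing height should be measured 5 times using a calibrated stadiometer. The average of the 5 measurements will be used as the outcome measure". For sitting height: "Sitting height should be measured three times using a seated stadiometer. The average of the 3 measurements will be used as the outcome measure". For arm span: "Head circumference and arm span will each be measured once using standard procedures". The same paragraph then defines the derived variable: "Arm span minus standing height will also be calculated". The footnotes to both schedules of activities in section 1.3 give repeat counts for standing and sitting height only.

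Arm span is used in two places:

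- **Secondary endpoint** (synopsis and section 3): "Change from baseline in arm span minus standing height after 12 months of treatment". Section 9.4.3 tests it in the same way as the primary efficacy endpoints, that is, by paired t-test.
- **Individual stopping criteria** (section 7.1): under clinically significant worsening of existing disproportion, one of the two listed measurements is arm span minus height, with the condition "Worsening of more than 1 standard deviation since initiation of therapy with a SDS either >+2 or <-2". Meeting a criterion temporarily stops that child's dosing and the DSMB is told. The Study Suspension Criteria extend this to all dosing, again temporarily, for: "Any two subjects with clinically significant worsening of existing disproportionate growth as defined above in the individual stopping criteria".

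The protocol gives no measurement-error figure for arm span and no numerical reference SD for the difference. It neither requires nor forbids re-measuring a surprising value.

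**The concern.** The protocol has two disproportion measures: sitting height ratio and arm span minus height. Both are secondary endpoints and both appear in the stopping criteria. The sitting-height component is replicated and averaged. The arm-span component is not; it is grouped with head circumference, which feeds no listed endpoint or stopping measurement. No reason is given for the difference.

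A difference is only as precise as its noisier part, so five height readings bring little if arm span is read once. Two things are at stake. One is the precision of the secondary endpoint, most of all in genetic cohorts of about 10. The other is how reliable the measured part of a safety trigger is. The criterion counts from the start of therapy, so an error in the Day 1 reading enters every later comparison for that child, including those in the extension. An analysis plan cannot recover readings that were never taken.

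**Working it through.** The protocol states no precision or error figure here, so there is nothing to reproduce. The check asks how much of the noise comes from the single reading and what three readings would change.

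**Inputs from the protocol:** 5 height readings averaged; 1 arm-span reading; 3 sitting-height readings as the model for the fix; trigger at more than 1 SD of worsening with SDS beyond +2 or -2; two children for the study-wide stop.

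**Assumptions (not in the protocol):** error SD of one height reading 0.3 cm; error SD of one arm-span reading (*a*) 0.3 to 1.0 cm; independent errors; reference SD of arm span minus height 2.5 to 3.5 cm; true between-child SD of the 12-month change (*b*) 1 to 2 cm; 25 children already beyond 2 SDS.

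**Step 1. Share of error variance at one visit.** Height contributes 0.3²/5 = 0.018. The arm-span share is *a*²/(*a*² + 0.018):

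- *a* = 0.3: 0.09/0.108 = 83%
- *a* = 0.5: 0.25/0.268 = 93%
- *a* = 1.0: 1/1.018 = 98%

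**Step 2. Error SD of the change between two visits**, with *k* arm-span readings at each: √[2(*a*²/*k* + 0.018)].

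| *a* (cm) | *k* = 1 | *k* = 3 | Reduction |
|---|---|---|---|
| 0.5 | √0.536 = 0.73 | √0.203 = 0.45 | 39% |
| 1.0 | √2.036 = 1.43 | √0.703 = 0.84 | 41% |

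**Step 3. Total SD of the change**, which is what the paired test uses: √(*b*² + error SD²).

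| *b* (cm) | *a* = 0.5: one to three readings | *a* = 1.0: one to three readings |
|---|---|---|
| 1.0 | 1.24 to 1.10 (12% less) | 1.74 to 1.30 (25% less) |
| 1.5 | 1.67 to 1.57 (6% less) | 2.07 to 1.72 (17% less) |
| 2.0 | 2.13 to 2.05 (4% less) | 2.46 to 2.17 (12% less) |

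At *a* = 1.0 and *b* = 1.5, the standard error of the mean change in a cohort of 10 is 2.07/√10 = 0.66 cm with one reading and 1.72/√10 = 0.54 cm with three.

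**Step 4. False triggers from reading error alone.** For a child already beyond 2 SDS with no true change, the chance per comparison is *p* = 1 − Φ(reference SD / error SD of change). The chance of two or more among 25 is binomial. With one reading:

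| *a* (cm) | Reference SD (cm) | *p* | Two or more of 25 |
|---|---|---|---|
| 0.5 | 2.5 | 0.03% | about 0.003% |
| 1.0 | 2.5 | 4.0% | 26% |
| 1.0 | 3.0 | 1.8% | 7.2% |
| 1.0 | 3.5 | 0.7% | 1.4% |

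With three readings at both visits, *a* = 1.0 and reference SD 2.5 cm, *p* is 0.1% and the chance of two or more is under 1%.

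**Step 5. Children who already have a single Day 1 reading.** With one reading on Day 1 and three later, the error SD of the change at *a* = 1.0 is √[(1 + 0.018) + (1/3 + 0.018)] = √1.369 = 1.17 cm. At reference SD 2.5 cm, *p* is 1.6% and the chance of two or more of 25 is 6.2%.

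**The case against.** The section is explicit and does not contradict itself. One reading is a choice, not a mistake. The noise is random, so it does not bias the mean change, and no primary endpoint uses arm span. The study is exploratory with no sample-size calculation. The 40% reduction concerns error SD only; the test sees 4% to 25%. Repeat readings at one visit may share a positioning error, which would shrink the gain. All of this stands and limits the weight of the point.

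A reader might infer that the rule is likely to stop the trial on reading error. The documents do not support that:

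- The 26% figure is one corner of assumed inputs. It falls to about 0.003% at 0.5 cm reading error, to 1.4% with a 3.5 cm reference SD, and to 5.8% if 10 rather than 25 children are beyond 2 SDS.
- A simulation over the 6- and 12-month visits in 75 children, with the SDS condition applied, gave 1% to 91% at 1.0 cm for two or more flags. The top of that range needs a 2.5 cm reference SD and a cohort centred at 2 SDS on this measure, and the protocol states neither.
- Both stops are temporary. After a study-wide stop the DSMB reviews within 5 to 7 days, and continuing as planned is a listed outcome.
- The criterion requires clinically significant worsening and gives the investigator's assessment a role. The and/or wording does not make that role mandatory, but neither does it say that one outlying reading triggers a stop automatically, as Step 4 assumes.

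What survives is that arm span is the weak component of a variable used twice, and that the protocol already treats the parallel measure better.

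**Conclusion.** The point holds as a minor, low-cost improvement in measurement. That the single reading dominates the error of the difference is robust: it holds even if arm span is read as accurately as height (83%). The gain for the endpoint is modest, a 4% to 25% smaller total SD of change over the assumed range. False triggers are negligible at 0.5 cm reading error and become possible near 1.0 cm, where two or more have a chance of about 1% to 26% with 25 children beyond 2 SDS and a reference SD of 3.5 down to 2.5 cm. Because those figures let the arithmetic alone fire the rule, they are upper-end illustrations for these inputs and not predictions. Reading error, reference SD, the number of children beyond 2 SDS and the true SD of change are all assumptions. Nothing here bears on whether the stopping threshold is right.

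**What to change.** In section 8.1, and in the anthropometry footnotes to both schedules in section 1.3, specify that arm span is measured three times at each in-person visit and that the mean is used, as for sitting height. Use that mean for the secondary endpoint and for the arm-span measurement in the disproportion criterion. Leave the criterion unchanged.

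The cost is two further readings by staff already measuring the child, a minute or two per visit, and two CRF fields. Children who already have a single Day 1 reading gain less: at 1.0 cm reading error their error SD of change falls from 1.43 to 1.17 cm rather than 0.84 cm. The number of readings behind each value should be recorded so that the analysis can tell the two groups apart.
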